### Statistical consideration

A total of 40 participants will be recruited, evaluated and analysed as part of this study. Analysis will be performed using an intention to treat approach [43]. A power analysis using PS Power and sample size calculations Version 3.1.2 has been performed to calculate the sample size required for this study, based on the primary outcome variable VO_2peak_ (ml kg min^−1^). In the absence of comparable published data in AYA patients, similar studies undertaken by Thorsteinsson et al. [44] and West et al. [45] in paediatric and adult patients demonstrated an effect size of 0.80. The standard deviation across multiple studies utilising VO_2peak_ as the primary outcome measure varies from 1.5 ml kg min^−1^ to 5.7 ml kg min^−1^, and therefore, a median value (3.6 ml kg min^−1^) has been utilised for this trial sample size calculation. Assuming a 5% significance level and a power of 0.8, a sample size of 36 patients (18 per group) will be required. An additional 10% has been included (*n*=4) to allow for attrition or unusable data. An interim analysis is planned following 50% of participant recruitment to investigate outcomes between groups.

Both interim and final analysis will employ standard descriptive statistics (M, SD, *n*, %) to summarise data on participant demographics and recruitment rates. Outcome analyses will include Student’s *t*-test, chi-square, correlation, regression and repeated measures ANOVA where relevant to examine differences between groups in the nominated variables, as well as the overall change scores over time. Further statistical analysis will be employed to investigate any associations between exercise-related changes and TRTs. Any clinically relevant covariates will be included in the analyses. All statistical analyses will be conducted using SPSS software (version 20.0, IBM, Armonk, NY, USA) and significance will be set at *p*≤0.05.

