### Primary outcome measure

The primary outcome of this RCT is cardiorespiratory fitness (V0_2peak_) as measured by a submaximal cardiopulmonary exercise test (CPET). The submaximal test will be conducted in a research setting by trained exercise specialists only, who will be blinded to the participant group allocation [31]. Participants will be instructed to follow their usual diet and incidental activity and abstain from formal exercise in the 24 h prior to testing. Additionally, the research team will review participants’ recent blood test results prior to assessments to ensure results are within the safe parameters for exercise [30]. Prior to commencing the test, participants’ resting heart rate and blood pressure will measured and a heart rate monitor will be attached to the participant (Wahoo Tickr heart rate monitor, Wahoo Fitness LLC, Georgia, USA). Target heart rate (THR) will be calculated using the formula (220 − age) [32] × 0.85 which will be used as criteria to terminate the test unless volitional exhaustion is met prior to this. Participants will be sat on a front access Exertech Ex-10 cycle ergometer (Repco Cycle Company, Huntingdale, Victoria, Australia) and familiarised with the testing protocol. The ramped protocol will have participants commence cycling at 20 watts (W) for 1 min and continue to increase by 20W per minute until they reach their THR or volitional exhaustion. Participants will complete the stage in which they reach their THR unless concluded prior to this. At the end of each minute, heart rate and RPE will be recorded [28]. Participants will complete a 3-min cool down on the bike pedalling with no resistance at a self-selected slow speed. Recovery heart rate and blood pressure will be recorded 10 min after the cessation of the test.

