During the test, participants will be required to breathe through a mouthpiece connected to a computerised gas analysis system. The system includes a ventilometer (Universal ventilation meter, Vacumed, Ventura, CA, USA) and oxygen and gas analysers (Ametek Applied Electrochemistry S-3A/1 and CD-3A, AEI Technologies, Pittsburgh, PA) which calculate minute ventilation (V_E_), respiratory exchange ratios (RER) and oxygen and carbon dioxide in expired air at 15-s intervals respectively. Calibration of the equipment will be conducted prior to and following each test using a standard reference gas of known concentration. Values at the conclusion of the test will be recorded in absolute (L/Min) and relative (mL/kg/min) terms. Predicted peak oxygen consumption (V0_2peak_) will be extrapolated using the participants’ heart rate (HR) and V0_2_ from two submaximal stages from the test where a steady state heart rate between 115 and 150 beats per minute is recorded. The slope will be calculated using the ratio of difference between the two submaximal V0_2_ measures and their corresponding heart rates and then be used to extrapolate to predicted maximal heart rate (220 − age) [32–35].

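### The planning SD of 3.6 ml/kg/min is called a median but equals the midpoint of the two values given, and 18 per group does not deliver the stated 80% power at the stated effect size

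*Protocol article*

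**What the plan says.** Statistical consideration in the Protocol article bases the calculation on VO2peak in ml/kg/min. It reports that earlier studies "in paediatric and adult patients demonstrated an effect size of 0.80", and prefaces this with "In the absence of comparable published data in AYA patients". On variability it refers to "The standard deviation across multiple studies utilising VO_2peak_ as the primary outcome measure" and says that this "varies from 1.5 ml kg min^−1^ to 5.7 ml kg min^−1^, and therefore, a median value (3.6 ml kg min^−1^) has been utilised". Only the two ends of the range are given. The number of studies and their individual SDs are not.

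At a 5% significance level and power of 0.8, the section arrives at 36 patients (18 per group), then adds 4 for attrition to reach 40. It states no difference in ml/kg/min and does not say whether the test is one- or two-sided.

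Primary outcome measure describes how the endpoint is obtained: "Predicted peak oxygen consumption (V0_2peak_) will be extrapolated using the participants’ heart rate (HR) and V0_2_ from two submaximal stages", with the line then carried to the age-predicted maximal heart rate.

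**The concern.** A median needs the individual values, and two extremes do not supply it. The sentence moves straight from the range to 3.6, and 3.6 is exactly halfway between the ends. A midpoint depends only on the smallest and largest SDs, here nearly four-fold apart (5.7/1.5 = 3.8), and says nothing about where most studies lie. Calling it a median gives it more empirical support than the text provides.

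The SD is also not shown to fit the trial's own comparison. The section concedes that comparable data in this age group are lacking, and the endpoint is a prediction from two submaximal stages, whose prediction error forms part of its variance.

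The SD turns a standardised effect into a difference in ml/kg/min that clinicians can judge. If its basis is unclear, and the power attached to 18 per group is overstated as well, readers will credit the trial with more ability to detect a benefit than it has. A null result could then be taken as evidence that exercise does not slow the decline in fitness.

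**Working it through.** **Inputs (Statistical consideration):** effect size 0.80; SD range 1.5 to 5.7; SD used 3.6 ml/kg/min; significance level 5%; power 0.80; 18 per group; 10% attrition. **Assumptions:** 0.80 is a standardised difference, and the test is a two-sided two-sample t-test.

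**1. Origin of 3.6.** (1.5 + 5.7)/2 = 7.2/2 = 3.6 exactly.

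**2. The plan's own sample size.** Raw difference implied by the stated inputs: 0.80 × 3.6 = 2.88 ml/kg/min.
- Normal approximation: n per group = 2 × (1.960 + 0.842)² / 0.80² = 24.5, so 25. The t-test needs 26. The total is 50 to 52, not 36.
- One-sided 5%: 20 (normal) or 21 (t) per group, total 40 to 42.
- Paired t-test on 0.80: 15 patients in total (12 one-sided).
- Reading 0.80 as a raw difference in ml/kg/min with SD 3.6: 318 per group.
- None of these gives 36. A pre-post correlation of about 0.55 with baseline adjustment (26 × (1 − 0.55²) ≈ 18), or about 0.65 with change scores (26 × 2 × (1 − 0.65) ≈ 18), would give 18 per group, but the article states no correlation.
- The attrition step does reproduce: 36/0.9 = 40.

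**3. Power at 18 per group with d = 0.80.** Noncentrality = d × √(n/2) = 0.80 × √9 = 2.40 on 34 degrees of freedom. Power is 64.5% (67.0% by the normal approximation). If all 40 are evaluable (20 per group), it is 69.3%. One-sided with 18 per group, it is 76.0%.

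**4. Effect for which 18 per group gives 80%.** Solving the noncentral t for power 0.80 gives d = 0.961. The normal approximation gives (1.960 + 0.842) × √(2/18) = 0.934.

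**5. Detectable difference = 0.961 × SD.**
- SD 1.5: 1.44 ml/kg/min
- SD 3.6: 3.46 ml/kg/min
- SD 5.7: 5.48 ml/kg/min

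**6. Role of the SD.** If 0.80 is held as a standardised effect, the SD cancels and power is 64.5% at SD 1.5, 3.6 and 5.7 alike. If a raw 2.88 is held fixed instead, power at 18 per group is over 99% at SD 1.5, 80% at 3.0, 64.5% at 3.6 and 31% at 5.7. This second set depends on an assumption that the document does not make.

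**The case against.** The strongest reply is that the SD hardly matters: on an effect size of 0.80 it drops out of the calculation, so median against midpoint is a matter of wording. This is right as far as it goes. A reader might infer that, within the plan's own range, power runs from over 99% down to 31%. The documents do not support that as a finding, because they state no raw difference; the spread appears only once 2.88, itself computed with 3.6, is held fixed. But the standardised reading does not rescue the 80% figure, since it gives 64.5% at every SD.

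Three other limits stand.
- A reader might infer that 3.6 cannot be the median. The individual SDs are not listed and might have that median, and with only two SDs the median and the midpoint coincide. What can be said is that the text does not show it.
- A reader might infer that no endpoint-specific variability was used. That is too strong, because the SDs are said to come from studies with VO2peak as primary outcome, in the trial's own units. What is not shown is a match to this population, measure and 10-week contrast.
- Whether the SDs are of levels or of changes may be set out in the full protocol, which is not shown. Its absence from the article is not held against the plan.

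It is also fair to say that a null result will be read from its confidence interval, which uses the observed SD. That reduces the harm but does not make the stated power correct.

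**Conclusion.** The point holds in limited form. The label is unsupported: 3.6 is the midpoint of the reported range and is not shown to be a median or to match this trial's contrast. The power statement is unsupported too. At the stated inputs, 18 per group gives about 64.5% rather than 80%, and 80% is reached only at about 0.96 SD, or 3.46 ml/kg/min at SD 3.6, against the 2.88 implied by 0.80. The power shortfall comes from the mismatch between 0.80 and 18 per group; the choice of 3.6 does not cause it. The SD determines what the detectable difference means in ml/kg/min: from 1.44 to 5.48 across the plan's own range.

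These figures assume a two-sided 5% two-sample t-test without baseline adjustment, with 0.80 as a standardised difference. A stated pre-post correlation or another planned test would change them. A reader might go further and conclude that the trial must be enlarged or sized on 5.7. The documents do not establish that: they give no reason to think the upper extreme is the right SD for this endpoint.

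**What to change.** In Statistical consideration:
- Describe 3.6 ml/kg/min as the midpoint of the published SD range.
- Keep 40 participants and 18 evaluable per group.
- Replace the 80% power claim with the difference detectable at 80% power with 18 per group (two-sided 5% t-test): 3.46 ml/kg/min at SD 3.6, with 1.44 and 5.48 at SDs of 1.5 and 5.7 as a sensitivity range.
- If power is also quoted for a fixed raw difference such as 2.88, state that difference and say that the power is conditional on it.

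This rewords one paragraph. It needs no extra patients and leaves conduct and analysis unchanged. The downside is that the plan will state a less favourable power than it does now.

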### Randomisation and blinding

As this is not a homogenous group, prior to randomisation, participants will be stratified according to intensity of their cancer treatment regimen: high intensity versus low/moderate intensity treatment. Table 2 demonstrates stratification of the most common cancers diagnosed in the AYA age range. Any participant recruited with a diagnosis not listed in Table 2 will be discussed within the research team and treating clinicians to determine the intensity of their treatment regimen. The division between low/moderate versus high intensity relates to the likelihood of low blood counts and degree of immunosuppression from the treatment regimen.

**Table 2 Tab2:** Stratification strategy of most common adolescent and young adult cancer diagnoses based on treatment regimen

Low/moderate intensity treatment diagnoses	High intensity treatment diagnoses
Hodgkin lymphoma	Acute lymphoblastic leukaemia
Germ cell tumours	Lymphoblastic lymphoma
Gynaecological tumours	Burkitt lymphoma
Non-Hodgkin lymphoma (excluding Burkitt)	Soft tissue and bone sarcoma
Melanoma	Squamous cell carcinoma of the head and neck

Following stratification, participants will be randomised via a computer-generated block randomisation (sealed envelope) procedure. The allocation sequence will be generated and maintained by a member of the research team that is not involved in patient contact or treatment. Both high and moderate intensity treatment groups will be randomised in block sizes of 4 and 8 into the two intervention groups: immediate exercise or usual care (delayed exercise) intervention. The block randomisation will allow for equal groups to be created by the end of the recruitment. Given the nature of the intervention, it is not possible to blind the investigators or the participants to their group allocation. However, the study personnel responsible for conducting primary outcome assessments will be blinded to participant group allocation.

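### The stated inputs require 26 participants per group, not 18; with 18 per group the power at the planning effect is about 64%, not 80%

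*Protocol article*

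**What the plan says.** All the inputs and the result stand in one paragraph of the article's Statistical consideration section.

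- **Effect size.** Two earlier studies are cited which "in paediatric and adult patients demonstrated an effect size of 0.80". No unit is attached.
- **SD.** Published values are said to range from 1.5 to 5.7 ml/kg/min, and "a median value (3.6 ml kg min^−1^) has been utilised for this trial sample size calculation".
- **Error rates and result.** "Assuming a 5% significance level and a power of 0.8, a sample size of 36 patients (18 per group) will be required".
- **Attrition.** Four more participants (10%) are added "to allow for attrition or unusable data", giving 40.

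The paragraph gives no sidedness, no target difference in ml/kg/min and no baseline or within-patient correlation. It does not say that the calculation used the crossover structure. The Background section sets the primary aim as a comparison with controls over a 10-week intervention, and the sample size is given per group. The Randomisation and blinding section plans equal groups.

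**The concern.** An effect size, a significance level and a power fix the sample size of a two-group comparison. An effect of 0.80 at 5% and 80% power leads to about 25 or 26 per group, so 18 is visibly too small.

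This paragraph is the article's only justification of the sample size for the primary outcome. If the stated power is too high, the risk of missing a real benefit at the authors' own planning effect is understated, and a non-significant result could be given more weight than the design supports. That matters here because the Discussion describes the trial as, to the authors' knowledge, the first randomised trial of its kind in this age group, and ties wide adoption of such programmes to its result.

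**Working it through.** **Inputs, all from Statistical consideration unless noted**

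- Standardised effect d = 0.80, so the implied difference is 0.80 × 3.6 = 2.88 ml/kg/min
- SD = 3.6 ml/kg/min
- Significance level 5%, taken as two-sided by convention because the article does not say
- Power 0.80
- Equal allocation (Randomisation and blinding)
- Figure to reproduce: 18 per group

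**Step 1. Normal approximation.** n per group = 2(z₀.₉₇₅ + z₀.₈₀)² / d² = 2(1.960 + 0.842)² / 0.64 = 24.5, rounded up to 25.

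**Step 2. Two-sample t-test (noncentral t).** The solution is 25.5, rounded up to 26 per group, where power is 80.7%. The stated 18 is not reproduced.

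**Step 3. Power at the stated size.** The noncentrality parameter is d√(n/2) = 0.80 × √9 = 2.40 on 34 degrees of freedom. Power is 64.5% (67.0% by the normal approximation). With 20 per group, so that all 40 are analysed, it is 69.3% (71.6% by the normal approximation).

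**Step 4. Other readings of the same inputs**

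| Reading | Requirement | Power at 18 per group |
|---|---|---|
| Two-sided t-test | 26 per group | 64.5% |
| One-sided 5% t-test | 21 per group (20.03 rounded up) | 76.0% |
| Paired, 0.80 on the within-patient difference | 15 patients in total | not applicable |
| Crossover, 0.80 on the between-patient SD, correlation 0 | 27 patients in total, fewer with positive correlation | not applicable |
| 0.80 as a raw difference in ml/kg/min (d = 0.80/3.6 = 0.222) | 319 per group | 9.9% |

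None of these gives 18 per group or 36 in total. The last row is included for completeness: the text calls 0.80 an effect size and gives it no unit, so the raw reading has little support.

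**Step 5. What 18 per group corresponds to.** Solving for the effect at 80% power gives d = 0.961. That is 0.961 × 3.6 = 3.46 ml/kg/min, or equivalently a difference of 2.88 with an SD of 2.88/0.961 = 3.0. The article states neither pair.

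**Step 6. Baseline adjustment.** If 0.80 is scaled to the cross-sectional SD, ANCOVA raises the effective d to 0.80/√(1 − ρ²), where ρ is the correlation between baseline and week 10. With 18 per group, power is 76.8% at ρ = 0.50, 79.7% at 0.55 and about 80.2% at 0.56. An unadjusted t-test on change scores uses 0.80/√(2(1 − ρ)) and gives only 70% at ρ = 0.56.

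**Step 7. The SD.** (1.5 + 5.7)/2 = 3.6, so the value called a median equals the midpoint of the quoted range. Holding the difference at 2.88 ml/kg/min with 18 per group:

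| SD (ml/kg/min) | d | Power | Needed per group for 80% |
|---|---|---|---|
| 1.5 | 1.92 | over 99% | 6 |
| 3.6 | 0.80 | 64.5% | 26 |
| 5.7 | 0.51 | 31% | 63 |

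**Step 8. Attrition.** 36/0.9 = 40, so this step is correct.

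**The case against.** The strongest reply is that the arithmetic shows a mismatch between inputs and result, not that the trial's true power is 64%. The article fixes neither the sidedness nor an unadjusted t-test. It also lists regression and repeated measures ANOVA, and says relevant covariates will be included. With a baseline correlation of about 0.56, ANCOVA would reach 80% power with 18 per group. An unreported input is also possible: a target of 3.5 ml/kg/min at SD 3.6 needs 17.6, so 18 per group, in which case 0.80 would only be background from the cited studies.

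This limits what can be said about the power of the eventual analysis, but it does not rescue the published figure. Neither the correlation nor the 3.5 ml/kg/min target appears in the article, and choosing a correlation because it makes 18 work is not a justification. If such an input was used, the paragraph is still wrong as written, and disclosing the input is the remedy.

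Two smaller points are fair. Sensitivity to the SD should be shown at both ends of the range, since the low end is very favourable. It also matters only if the target is a fixed difference in ml/kg/min; if 0.80 is a purely standardised target, the SD does not enter. The word median cannot be disproved without the individual study SDs, and on its own it is minor.

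**Conclusion.** The concern holds. From the declared inputs the requirement is 26 per group (52 evaluable), against a stated 18 per group (36). Power at 18 per group is 64.5%, so the chance of missing the planned effect is 35.5% rather than 20%. If all 40 are analysed, power is 69.3%.

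These figures assume a two-sided 5% test, a parallel comparison of the two groups, and 0.80 as a standardised effect on the scale of the analysed outcome. The first two are the conventional reading of a per-group size for a comparison with controls. The conclusion that 18 does not follow is less dependent on them, because the one-sided and paired alternatives fail too. Only an input absent from the article recovers 18 per group.

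This should be corrected, because it is a definite statement about the primary outcome that its own numbers contradict.

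**What to change.** First establish what was entered in the software: the target difference, the SD of the analysed quantity, the sidedness and any correlation. Then take one of two routes.

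1. **Restate the power.** Suggested wording: *With 36 evaluable participants (18 per group), a two-sided 5% t-test has 64% power for a standardised difference of 0.80 (2.88 ml/kg/min at SD 3.6); 80% power corresponds to 0.96 (about 3.5 ml/kg/min).*
2. **Declare the missing input.** If the calculation rests on baseline-adjusted ANCOVA, name that as the primary analysis and state the baseline to week-10 correlation (at least about 0.56 for 80% power with 18 per group), with a source independent of this calculation. If it rests on a larger target difference, state and justify that difference.

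On either route, describe 3.6 as the midpoint of the range unless the individual study SDs show it to be their median, and give power across SDs from 1.5 to 5.7 ml/kg/min.

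The cost is one rewritten paragraph and a less favourable, or openly conditional, power statement. No extra patients are needed. Keeping 80% power at 0.80 with an unadjusted two-sided test would instead take 52 evaluable participants, or 52/0.9 = 58 recruited rather than 40.

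### The plan permits but does not commit to adjusting VO2peak for baseline and the treatment-intensity stratum, so a less efficient primary test stays open in a 40-patient trial

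*Protocol article*

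**What the plan says.** All references are to the protocol article.

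- **Statistical consideration** lists the outcome methods as Student's t-test, "chi-square, correlation, regression and repeated measures ANOVA where relevant to examine differences between groups in the nominated variables", and adds overall change scores over time. It does not say which of these is the primary analysis of VO2peak. A further sentence says that covariates judged clinically relevant will enter the analyses, without naming any.
- **Randomisation and blinding** calls the patient group heterogeneous and for that reason says "participants will be stratified according to intensity of their cancer treatment regimen", with two levels (high; low/moderate).
- **Abstract, Methods/design** has the cardiopulmonary exercise test at 0, 10 and 20 weeks, so every participant should have a baseline VO2peak.
- **Discussion** names the only specific covariate in the article: physical activity that participants record during the trial.
- On size, Statistical consideration cites earlier studies that "in paediatric and adult patients demonstrated an effect size of 0.80", takes an SD of 3.6 ml/kg/min, and concludes: "Assuming a 5% significance level and a power of 0.8, a sample size of 36 patients (18 per group) will be required". A 10% allowance then brings the total to 40.

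**The concern.** The design supplies two natural adjustment terms at no cost: the baseline value of the primary outcome and the factor used to stratify randomisation. Neither is named as a model term. The one covariate that is named, recorded activity, is measured after randomisation. It may itself respond to allocation, because the Exercise prescription section encourages participants to do aerobic exercise outside the supervised sessions and to log it. Adjusting for it could remove part of the effect being estimated.

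At stake is precision in a small trial. The listed methods can differ a good deal in power on the same data, and the text does not say which will carry the primary conclusion. Naming the model and its terms in advance would also settle the choice among several plausible analyses.

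**Working it through.** **Inputs from the article:** 5% significance (taken as two-sided; the text does not say), effect size 0.80 (read as standardised), SD 3.6 ml/kg/min, 18 evaluable per arm. **Assumed, not in the article:** the correlation ρ between baseline and week-10 VO2peak, shown from 0.3 to 0.8. Week 10 is used because it is the last assessment before the arms cross over.

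**1. The plan's own figure.** For two independent groups with d = 0.80, two-sided 5% and 80% power, the need is 25 per arm (normal approximation) or 26 per arm (t distribution). The stated 18 per arm is not recovered. At 18 per arm the noncentrality is 0.80 × √(18/2) = 2.40 on 34 degrees of freedom, which gives power 64.5%. The step from 36 to 40 does reproduce: 36/0.9 = 40.

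**2. Relative variances.** With equal SDs at both visits, and the variance of the week-10 value set to 1:
- t-test on week-10 value: 1
- change score: 2(1 − ρ)
- ANCOVA on baseline: 1 − ρ²
- ANCOVA relative to change: (1 − ρ²)/[2(1 − ρ)] = (1 + ρ)/2

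With two time points, the group-by-time test of repeated measures ANOVA is the t-test on change. ANCOVA therefore has smaller residual variance than change at any ρ below 1, and change is worse than the raw week-10 value when ρ is below 0.5.

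**3. Power if d = 0.80 is scaled to the SD of values.** The effective effect is 0.80/√(relative variance). Degrees of freedom are 34 for the t-tests and 32 for ANCOVA with baseline and stratum. The stratum is charged its degree of freedom but credited with no explained variance.

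| ρ | Week-10 t-test | Change score | ANCOVA |
|---|---|---|---|
| 0.3 | 64.5% | 50.4% | 68.4% |
| 0.5 | 64.5% | 64.5% | 76.6% |
| 0.6 | 64.5% | 74.1% | 82.9% |
| 0.7 | 64.5% | 85.3% | 90.3% |
| 0.8 | 64.5% | 95.8% | 97.2% |

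Worked case, ρ = 0.6: change 0.80/√0.80 = 0.894; ANCOVA 0.80/√0.64 = 1.00.

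Over ρ = 0.5 to 0.7, ANCOVA cuts residual variance by 25% to 49% against the raw week-10 value, but by only 25% to 15% against change.

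**4. Power if 3.6 is the SD of change.** The change score then has d = 0.80 and 64.5% power whatever ρ is. The ANCOVA effect is 0.80/√((1 + ρ)/2):

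| ρ | Change score | ANCOVA |
|---|---|---|
| 0.3 | 64.5% | 82% |
| 0.5 | 64.5% | 77% |
| 0.6 | 64.5% | 74% |
| 0.7 | 64.5% | 71% |
| 0.8 | 64.5% | 69% |

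**5. Stratum.** The article does not say how strongly treatment intensity predicts VO2peak. Purely as illustration, if the stratum alone explained 5%, 10% or 20% of the variance, power at 18 per arm would be 66.6%, 69.0% or 74.0%, against 64.5% unadjusted.

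**The case against.** A reader might infer that the listed tests ignore baseline. The article does not support that. A change score subtracts baseline, and repeated measures ANOVA includes the baseline visit. Only a t-test on the week-10 value discards it, and that test is nowhere called primary; the stated aim, a smaller decline in fitness, points towards change. Regression is also on the list, and the covariate sentence would admit both baseline and stratum. This part of the objection stands, so the point is limited to adjustment being optional.

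A reader might also infer that covariates will be picked after outcomes have been seen, since the rule is open and a between-group interim analysis is planned. The text does not say so, and a full protocol or analysis plan that is not shown may fix the list.

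On size, three cautions stand:
- The larger variance cut applies only against the raw week-10 value. Against change, the power gain falls to 1 or 2 points at ρ = 0.8 when d is scaled to the SD of values.
- ANCOVA is not the only route to 80%: change exceeds it at ρ = 0.7 on that scaling.
- Ignoring the stratum costs precision only if the stratum is prognostic. It is defined by expected blood counts and immunosuppression, and no link to VO2peak is quantified.

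That model terms are often left to an analysis plan does not dispose of the point. The article does state a menu and a covariate rule, and a better method is available from data already being collected.

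**Conclusion.** The point holds as a recommended improvement in efficiency and pre-specification. It is not an error that invalidates the trial: an unadjusted comparison of randomised groups remains valid.

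At 18 per arm, with d scaled to the SD of values, ANCOVA gains about 4 to 33 points of power over the week-10 t-test (ρ = 0.3 to 0.8). Over change it gains about 18, 12, 9, 5 and 1 points at ρ = 0.3, 0.5, 0.6, 0.7 and 0.8. If 3.6 is the SD of change, the gain over change runs from about 18 points at ρ = 0.3 down to 4 or 5 at ρ = 0.8, and ANCOVA reaches 80% only at the lowest correlation tried. ANCOVA had the higher power than change at every value in both readings.

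The direction is therefore firm, while the size rests on an assumed ρ, on which SD the 3.6 represents, and on equal SDs at both visits. No figure can be put on the stratum's gain from the document.

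**What to change.** 1. Name the primary analysis: linear ANCOVA of week-10 VO2peak (ml/kg/min) on arm, baseline VO2peak and treatment-intensity stratum (high against low/moderate), reporting the adjusted difference with its 95% confidence interval.
2. Use the same form for each continuous secondary outcome, with that outcome's own baseline.
3. For the primary model, replace the open covariate sentence with these two terms.
4. Reconcile this with the Discussion section: move physical activity recorded during the trial to a supplementary analysis, and state that it is measured after randomisation and may be affected by allocation.
5. State whether 3.6 ml/kg/min is the SD of values or of change, so that the expected gain can be judged.

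The cost is two residual degrees of freedom (34 to 32 at 18 per arm) and a change of wording. It needs no extra patients, visits or measurements, and the SPSS software already named can fit the model.
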